The implementation of SMS in population-based cancer screening programs will improve participation, especially in CRC screening, will allow better management of resources, and will reduce costs in both programs.

Specific hypotheses:

Sending SMS reminder will have a greater impact on participation than the standard reminder (letter) in the CRC screening program.

The effect of SMS reminder on CRC screening will be greater among individuals who have been invited for the first time and who have not previously participated.

Participation after receiving SMS invitation in BC screening will be equal to or better than the invitation by letter.

The option that includes the sending of SMS will be cost-effective in comparison to the current method used.

OBJECTIVES

Main Objective

To evaluate the effectiveness of SMS in population-based cancer screening programs in the Metropolitan Area of Barcelona.

Specific objectives

To analyze the effect of SMS reminders in a CRC screening program.

To analyze the effect of SMS reminder on participation in a CRC screening program by previous screening behavior (non-participants, new participants, previous participants) and residing in areas of limited postal access.

To assess the impact on participation and cost reduction of SMS FIT return reminder in a CRC screening program.

To analyze the impact on successive participation of receiving an invitation to the BC screening program by SMS.

To evaluate the usefulness of SMS as an appointment re-scheduling tool for screening mammograms.

To analyze the cost-effectiveness of the three SMS interventions, two in the CRC screening program and one in the breast screening program in relation to the current intervention.

INTERVENTIONS

Intervention 1: Invitation reminder for CRC screening.

Design and study population

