Randomized controlled trial. All women aged 52-69 who have participated in the BC screening program in the immediately preceding round and have a mobile phone number registered in the HealthCare Database.

Sample size

About 80,000 women are invited each year, half of whom participated in the previous round. As the invitation in the program is not made by basic health area but by date of birth, the assignment to the intervention groups will be made by a simple random allocation. Women whose mobile number is not available will receive the invitation letter but will not be included in the study. An interim analysis will be performed two months after the start of the trial, and the trial will be stopped if timely participation in the group invited by SMS compared to the guest by letter is reduced by 3% or more.

Variables

The dependent variable will be participation or not in the screening 8 weeks after the initial date of invitation to the program. Invitation (SMS/letter) will be independent variable and other variables will be collected: previous screening behavior, accessibility to postal mail and socio-demographic variables (age and AQUAS-social index).

Analysis

Logistic regression models will determine if the SMS invitation has an equal or better participation than the letter invitation.

Process evaluation

All three interventions will include a process evaluation. We will use a mixed-methods study design, including a survey (n=100 for each intervention) to test reading and understanding of text messages among participants, and qualitative interviews to explore participants’ experiences of the interventions (with an estimated sample of n=36 for interventions 1 and 2, and n=24 for intervention 3). Findings from the process evaluation will inform interpretation of outcomes and any variation of effects in subgroups as well as strategies to refine and optimize the tested interventions.

Cost-effectiveness analysis

The cost-effectiveness analysis will be done through a Decision Tree for each of three interventions that will take into account the use of SMS on costs and results.

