Healthcare financer perspective will be analyzed. Following healthcare costs will be included, which will be evaluated in the population-based screening programs: a) Labor costs, consumables and depreciation of property, facilities and equipment, as well as "overheads". The SMS alternative will specifically include the personnel and infrastructure fixed costs; b) Diagnosis costs, specifically the costs of evaluating cases with a positive screening test. Future costs will not be included.

The effectiveness will be measured through the number of people who have participated in the screening and, if applicable, the proportion of advanced malignancies detected by increased participation will be calculated.

The result will be specified as an incremental ratio between costs and effectiveness (ICER) which was defined as cost per participants. The temporary period of analysis will be 1 year. A deterministic sensibility analysis will be applied to test the robustness of the results.

LIMITATIONS

Among the limitations of the study, we highlight that in order to incorporate SMS as a new communication tool; the proportion of users with a correct number must be high. We are able to access the mobile phone number of more than 85% of the eligible population and this proportion is increasing year after year.

In addition, in two previous studies that we carried out in both BC and CRC cancer screening, the proportion of wrong numbers was 9-10%.

The size of the SMS might be a limitation, as it has to be limited to 160 characters. However, we can add a link to more detailed information on the screening process. Example: ICO reminds you of the importance of preventing RCC. If you want to take the test, go to: <https://zmz.es/dKmBlg>

Ethical aspects

The Catalan Institute of Oncology the entity responsible for the processing of personal data of men and women between 50 and 69 years of age in the southern metropolitan area of Barcelona invited to participate in population programs for the early detection of cancer, is in the process of adjusting and updating its protocols, arrangements, conventions, terms, ..., to respond adequately to new regulations on confidentiality and protection of personal data (Regulation 2016/679 of the European Parliament and Council of 27 April 2016 on the protection of individuals (RGPD) and Law Organic Law 3/2018 of 5 December on the Protection of Personal Data and Guarantee of Digital Rights (LOPD-GDD).

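### Intervention 3 poses an equal-or-better question but sets no non-inferiority margin, scale or power, so its logistic regression has nothing to establish *equal* against

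*Protocol*

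**What the plan says.** The specific hypothesis for breast screening (Protocol, Hypothesis) is: "Participation after receiving SMS invitation in BC screening will be equal to or better than the invitation by letter". The Analysis section of Intervention 3 is one sentence: "Logistic regression models will determine if the SMS invitation has an equal or better participation than the letter invitation".

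The Sample size section of Intervention 3 describes the available population and the allocation: "About 80,000 women are invited each year, half of whom participated in the previous round", and "the assignment to the intervention groups will be made by a simple random allocation". It contains no calculation. It gives no target number, alpha, power, expected participation or difference of interest. By contrast, Intervention 1 states a 3% difference, 5% alpha and 80% power, and Intervention 2 states 92% power for a 3% difference.

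The one tolerance given for Intervention 3 is the interim rule at two months. The trial stops if timely participation "in the group invited by SMS compared to the guest by letter is reduced by 3% or more". The text does not say whether 3% means percentage points or a relative reduction, and it does not carry the figure over to the final analysis.

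**The concern.** A claim that a new invitation is at least as good as the old one needs a stated loss that would still be acceptable. Without it, the default reading of a logistic regression is a test of odds ratio 1, and neither outcome of that test answers the question. A non-significant result is not evidence of equality. A significant deficit may be too small to matter.

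Which of these happens then depends on how many women are analysed and not on what loss of participation the programme can tolerate. A margin chosen after the results are known would carry little weight. A margin also defines the hypothesis and what counts as success, so it is not routine modelling detail that a protocol can leave to the analysis plan.

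**Working it through.** The plan has no calculated figure for Intervention 3 to reproduce. The check therefore asks what a test of odds ratio 1 would do at the size the documents imply, and what a margin would require.

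**Inputs from the protocol**
- About 80,000 women invited a year, half of them prior participants: 80,000 × 0.5 = 40,000 (Intervention 3, Sample size).
- "We are able to access the mobile phone number of more than 85% of the eligible population" (Limitations): 40,000 × 0.85 = 34,000, or 17,000 per arm.
- In earlier studies "the proportion of wrong numbers was 9-10" per cent (Limitations): 34,000 × 0.90 = 30,600, or 15,300 per arm. This is used only as a cautious lower size, not as a proposed analysis set.

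**Assumptions, not in the protocol for Intervention 3**
- 1:1 allocation and one year of accrual.
- The 85% applies to prior breast screening participants.
- Letter participation *p* of 70-95%.
- Two-sided 95% intervals.
- For non-inferiority power, a true difference of zero.

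**Step 1. Precision.** SE = √(2p(1−p)/n), and the 95% half-width is 1.96 × SE. For p = 0.70 and n = 17,000, SE = √(0.42/17,000) = 0.497 points and the half-width is 0.97 points.

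| p | SE (points) | half-width (points) |
|---|---|---|
| 0.70 | 0.497 | 0.97 |
| 0.80 | 0.434 | 0.85 |
| 0.85 | 0.387 | 0.76 |
| 0.90 | 0.325 | 0.64 |
| 0.95 | 0.236 | 0.46 |

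An observed deficit just above the half-width is significant. That is about 0.6-1.0 point at 70-90% participation, and about 0.5 at 95%.

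**Step 2. How often a small true loss would be significant.** With 17,000 per arm, a true 1-point loss reaches significance with probability 52% at p = 0.70, 72% at 0.85 and 98% at 0.95. If the interim 3% is absolute, that loss is a third of it.

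**Step 3. What a non-significant result would hide at this size.** A non-significant deficit is smaller than 1.96 × SE, so its lower 95% limit is no worse than −2 × 1.96 × SE. At 17,000 per arm this is −1.3 points (p = 0.90) to −1.95 points (p = 0.70). A 3-point loss would be excluded.

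**Step 4. What a non-significant result would hide in a smaller trial.** The protocol fixes no final number. As illustration only, at p = 0.85 the power to detect a true 3-point loss is 25% with 500 per arm, 44% with 1,000 and 73% with 2,000.

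**Step 5. Power with a margin.** Power = Φ(margin/SE − 1.96).
- Absolute 3-point margin, least favourable case (p = 0.70, n = 15,300): SE = √(0.42/15,300) = 0.524 and Φ(3/0.524 − 1.96) = Φ(3.77), above 99.9%. Power is higher at every other *p* up to 95%, and at 17,000 per arm.
- If 3% is relative, the margin at p = 0.70 is 0.03 × 70 = 2.1 points, and power is 98% at 15,300 per arm and 99% at 17,000.

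**Step 6. Scale.** An absolute 3-point loss corresponds to an odds ratio of 0.87 at p = 0.70, 0.80 at 0.85 and 0.61 at 0.95. A margin therefore has to be stated with its scale.

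**The case against.** The strongest reply is that the trial is too large for the feared error. Step 3 bears this out: at about 17,000 per arm, any non-significant deficit already excludes a 3-point loss. A reader might infer that the plan risks accepting SMS despite a loss of that size. At the implied size it does not. The qualification is that this size is a derived pool, not a number the protocol commits to.

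It can also be said that calling a small real deficit worse is strict rather than invalid, because the hypothesis is worded as equal or better. That is fair as far as it goes. However, the plan itself continues the trial at interim for any observed loss below 3%, so a final reading that fails SMS for under 1 point sits badly with its own tolerance if that 3% is absolute.

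Three stronger readings are not supported:
- **That logistic regression is the wrong model.** It can support non-inferiority through its confidence limit once a margin exists.
- **That the protocol equates non-significance with equality.** It states no decision rule. The detailed rule and sidedness may be in an analysis plan that is not shown.
- **That replacing the letter hinges on this test alone.** The background on breast screening puts better use of resources first, and a cost-effectiveness analysis and a process evaluation are also planned.

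Nor does the interim trigger serve as the missing margin. It acts on the observed difference at two months, on an unstated scale, and is not linked to the final analysis.

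**Conclusion.** The point holds in a limited form. Intervention 3 states a non-inferiority hypothesis and names the model that will decide it, but omits the margin, its scale and any power statement. As written, *better* can be tested and *equal* cannot. At the implied size the practical risk is mainly that an observed deficit of about 0.6-1.0 point is significant and read as failure. A second risk is that no final number is fixed to secure the precision that makes a non-significant result informative.

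The figures rest on the assumptions listed above. The power figures are the most exposed, because they take the true difference as zero. The documents do not say what happens to women in the SMS arm whose number is wrong. If some go uninvited, the true difference could be below zero and power would fall: with a true 1-point loss, power for an absolute 3-point margin is 97% at p = 0.70 and 15,300 per arm.

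**What to change.** In the protocol section on Intervention 3:

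1. State the hypothesis as non-inferiority of SMS to letter on the difference in 8-week participation among all randomised women, keeping those with wrong numbers in their assigned arm.
2. Fix a margin in advance and justify it by the loss of participation the programme could accept, not by what the sample size can afford. It should be no wider than the 3% that the plan already treats as unacceptable. State whether that 3% is absolute or relative, and how the margin relates to the interim trigger.
3. Conclude equal or better only if the lower limit of the two-sided 95% confidence interval for SMS minus letter lies above minus the margin. The estimate may come from the logistic model by standardisation. If non-inferiority is shown, test superiority next; this ordered step needs no alpha adjustment.
4. Add a power statement that labels its assumptions: allocation ratio, accrual period, letter participation, share with a mobile number, wrong numbers and assumed true difference.

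The cost is about a paragraph of text, repeated in the analysis plan. No extra women are needed under the assumptions shown.
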